#### Experimental intervention: immediate necrosectomy following EUS-guided drainage of WON

In the immediate necrosectomy group, DEN will be initiated during the same session of the initial EUS-guided drainage or at least within 72 h of the drainage. DEN will be performed using a gastroscope, and the devices (e.g. biopsy forceps, snare, or basket catheter) used during the DEN are determined on the endoscopist’s discretion. The DEN procedures will be repeatedly performed until clinical success.

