### Outcomes {12}

Table 1 summarises the primary and secondary outcome measures in the WONDER-01 trial. The primary endpoint is time from randomisation to clinical success. Clinical success is defined as (1) a decrease in a WON size to 3 cm or less and (2) an improvement of at least two out of the three inflammatory markers (i.e. body temperature, white blood cell count, and C-reactive protein). Patients who do not undergo clinical success within 6 months of the randomisation are treated as cases with clinical failure. We will evaluate time to clinical success as the primary endpoint as this outcome measure is correlated with duration of intensive treatment and thus a burden on patients and the health care system. The median time to clinical success will be used to evaluate the overall treatment efficacy of a given intervention. Other outcomes will be summarised as medians (interquartile ranges) or mean ± standard deviations, as appropriate, for continuous variables and number (percentage) of patients for categorical variables.

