### Sample size {14}

For the sample size calculation, we assumed that the rates of clinical success at 60 days of the initial EUS-guided drainage were 60% in the immediate necrosectomy group and 35% in the step-up approach group according to preliminary data from a retrospective analysis by the WONDERFUL study group (under submission). When we planned 36 months for patient accrual and 6 months for follow-up, 64 patients were required with a two-sided α level of 0.05 and a power of 0.80. Taking the dropout into account, we planned a sample size of 70 patients (35 patients per arm).

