## Data collection and management

### Plans for assessment and collection of outcomes {18a}

Clinical parameters at baseline and outcome variables have been pre-defined. To promote the quality of data on the primary endpoint (i.e. clinical success), the expert panel will review the clinical course and CT images upon request. Data on those variables will be collected from the electronic medical chart at each centre. The schedule of enrolment, randomisation, interventions, and assessments is summarised in Table 3.

**Table 3 Tab3:** Schedule of interventions and assessments in the WONDER-01 trial

	Study period					
	Pre-intervention	Intervention (within 6 months of randomisation)				Post-intervention
	≤ 10 days before randomisation		Within 3 days of randomisation	7 days after intervention	Clinical success	After five years of clinical success
	Screening	Randomisation	Intervention		Assessment	Follow-up
Informed consent	X					
Eligibility screening	X					
Assessment of WON	X					
Assessment of symptoms	X				X	
Body temperature	X			X	X	
Blood test^a^	X			X	X	
Imaging study^b^	X			X^c^	X	
Electrocardiogram	X					
Randomisation		X				
Interventions			X			
Assessment of primary endpoint					X	
Assessment of secondary endpoints				X	X	X
Monitoring of adverse events				X	X	X

^a^A blood test includes the following items: white blood cell count, haemoglobin, platelet count, albumin, aspartate aminotransferase, alanine aminotransferase, gamma-glutamyl transpeptidase, alkaline phosphatase, total bilirubin, amylase, lipase, blood urea nitrogen, creatinine, C-reactive protein, and international normalised ratio of prothrombin time

^b^Contrast-enhanced computed tomography is performed unless there are contraindications for contrast use. Magnetic resonance imaging may be performed on the investigator’s discretion

^c^Imaging studies are performed at least every 2–3 weeks during the intervention period

Abbreviation: *WON* Walled-off necrosis

The investigators at each centre will collect relevant patient data from the electronic medical chart and input anonymised data to the trial database. The standardised trial database has been constructed using the Microsoft Access software (Microsoft Corp., Tokyo, Japan) and has been distributed to participating centres. The database file will be uploaded to the online storage that can be accessed only by the investigators.

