## Statistical methods

### Statistical methods for primary and secondary outcomes {20a}

In the primary analysis, we will compare times to clinical success between the immediate necrosectomy and step-up approach groups. In our primary hypothesis testing, cumulative survival probabilities of times to clinical success will be estimated using the Kaplan–Meier product-limit method and be compared using the log-rank test. Patients are censored at the time-point of salvage surgery, the last follow-up, 6 months of the randomisation, or death, whichever came first. In the secondary analyses, we will use Student’s *t*-test or Wilcoxon rank-sum test, as appropriate, for continuous variables; the chi-square test or Fisher’s exact test, as appropriate, for categorical variables; and the log-rank test for time-to-event variables.

The two-sided α level of 0.05 was used for statistical significance for all analyses. All analyses will be conducted for the intention-to-treat population, and examinations of per-protocol population will represent secondary analyses.

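### The scans that date clinical success have only a variable minimum interval, which need not be the same in the two arms

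*Protocol article*

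**What the plan says.** The Outcomes section {12} states: "The primary endpoint is time from randomisation to clinical success". Success has two parts. One is "a decrease in a WON size to 3 cm or less"; the other is improvement in at least two of temperature, white cell count and C-reactive protein.

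Table 3 (section {18a}) places imaging at screening, 7 days after intervention, and in a column named for clinical success itself, which has no calendar date. Footnote c adds the only rule for repeat scans: "Imaging studies are performed at least every 2–3 weeks during the intervention period". No section counts scan days from randomisation, limits extra scans or requires equal intervals in the two arms.

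In section {20a}, times to success are to be "estimated using the Kaplan–Meier product-limit method and be compared using the log-rank test". Section {17a} leaves participants and investigators unblinded, and blinds outcome evaluators and data analysts.

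**The concern.** Shrinkage to 3 cm happens at an unseen moment between two scans. Unless the markers are the last component to be met, the recorded date is that of the first scan to show it. On average the recorded date is therefore late by about half the scan interval. If both arms share the interval, the delay is common and cancels. If they do not, the difference in delay enters the primary comparison as an apparent treatment effect, and more patients do not remove it.

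The schedule leaves room for such a difference. The interval is open at the short end and loose at the long end, those treating the patient know the allocation, and the care paths differ. In the experimental arm, "The DEN procedures will be repeatedly performed until clinical success", so someone must keep checking for success. The control arm moves through an observation period, then drainage steps, then on-demand necrosectomy. Blinded evaluators protect the reading of a scan, not the day on which it was taken.

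**Working it through.** **Inputs from the protocol.** Success at 60 days of "60% in the immediate necrosectomy group and 35% in the step-up approach group"; 36 months of accrual and 6 months of follow-up; two-sided α 0.05; power 0.80; 64 patients, raised to 70 (35 per arm) for dropout (Sample size {14}). Censoring: "Patients are censored at the time-point of salvage surgery, the last follow-up, 6 months of the randomisation, or death, whichever came first".

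**Reproducing the plan's figure.** With exponential times, the hazard is λ = −ln(1 − p)/60.
- Hazard ratio: ln(0.40)/ln(0.65) = 2.127.
- Medians, ln 2/λ: 45.4 days (experimental) and 96.5 days (control).
- Freedman events: (1.96 + 0.842)² × [(2.127 + 1)/(2.127 − 1)]² ≈ 60.4, so 61.
- The average event probability under uniform accrual with follow-up to study end is 0.981. 61/0.981 = 62.2, or 32 per arm, so N = 64. This matches.

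**Expected shift.** Mean detection delay is about half the interval, so the shift is about half the difference between intervals: (21 − 14)/2 = 3.5 days, and (21 − 7)/2 = 7 days.

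**Simulation.** The arm-specific intervals are assumptions. The settings were 35 per arm, exponential true times, first scan at day 7, later scans at the arm's interval with ±2 days of jitter, success dated at the first scan after true resolution, a cap at day 182, and 1,500 runs per setting. There is no true difference. A false win is a significant log-rank result favouring the first-named arm (nominal 0.025). The shift is first minus second arm.

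| Interval (days) | True success at 60 days, both arms | Median shift (days) | Two-sided error | False win |
|---|---|---|---|---|
| 14 v 14 | 60% | −0.3 | 0.057 | 0.027 |
| 21 v 21 | 60% | +0.3 | 0.052 | 0.027 |
| 14 v 21 | 60% | −3.6 | 0.056 | 0.043 |
| 7 v 14 | 60% | −3.4 | 0.052 | 0.040 |
| 7 v 21 | 60% | −7.0 | 0.087 | 0.078 |
| 14 v 14 | 35% | +0.2 | 0.047 | 0.025 |
| 21 v 21 | 35% | −0.6 | 0.052 | 0.025 |
| 14 v 21 | 35% | −3.1 | 0.061 | 0.035 |
| 7 v 14 | 35% | −3.3 | 0.050 | 0.034 |
| 7 v 21 | 35% | −6.9 | 0.055 | 0.041 |

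The Monte Carlo standard error is about 0.4 point at 2.5% (√(0.025 × 0.975/1500)) and 0.6 point at 5%. In most unequal settings the total error hardly moves; what changes is that false positives collect on one side.

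A separate set of 4,000 runs per setting used a common median of 62 days, the value implied by averaging the two planned hazards. It gave false-win rates of 0.040–0.051 for 14 v 21 days and 0.051–0.088 for 7 v 21 days. In each range the lower figure is for randomly phased scans and the upper for aligned scans.

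**Under the planned effect** (60% v 35%, 70 patients), by experimental/control interval: power is 0.81 at 14/14, 0.85 at 14/21, 0.89 at 7/21 and 0.70 at 21/7.

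**The case against.** A reader might infer that the experimental arm will be scanned more, so that the trial is tilted towards immediate necrosectomy. The documents do not support this. Observation in the control arm lasts 72–96 h of a 6-month window. After that, patients without enough improvement have stents replaced or added, further EUS-guided drainage or percutaneous drainage, and section {6b} itself presents this care as intensive. Those steps could call for as much imaging as repeat necrosectomy, or more. Nor does footnote c grant investigators discretion over frequency; Table 3 mentions discretion only for the use of MRI. The freedom comes from the wording of the minimum.

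Other points also carry weight. A 14 v 21 day contrast puts each whole arm at opposite ends of the stated range, and 7 days appears nowhere as a regular interval. Where markers improve after size, scan timing matters less. The article gives no dating rule, and the full protocol may hold one. Both arms share the 7-day scan and the same loose maximum interval, which limits the gap.

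These points remove any settled direction and keep the size small. They do not remove the mechanism: nothing stated makes scan timing equal between arms, and an analysis plan cannot recover scans that were not taken on common days.

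**Conclusion.** The point holds as a conditional and modest one. If scan frequency differs by arm, in either direction, the primary comparison is biased towards the more-scanned arm. For 14 v 21 days the shift is about 3–4 days and the one-sided false-win rate about 3.5–5%, against 2.5%. For the assumed extreme of 7 v 21 days, the figures are about 7 days and about 4–8%, with one aligned-scan run at 0.088.

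Against an implied gap of about 52 days between planned medians (97 − 45), this could not by itself produce the planned effect. It could decide a borderline result, change power by about −11 to +7 points in the extreme settings, and distort the median time to success, which section {12} names as the measure of overall efficacy.

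The figures rest on exponential times, on dating success at the scan, and on assumed intervals. The sample size of 64 is not in question here.

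**What to change.** For patients still to be enrolled:
- Set one imaging interval within the existing 2–3 weeks, on the same days from randomisation in both arms, with a stated window.
- Date the primary endpoint only from these scheduled assessments (scan plus markers). Unscheduled scans stay free for care but do not set the date.

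For all patients, including those recruited since 29 July 2022 under the present schedule:
- Add a sensitivity analysis that treats each success as interval-censored between the last scan without it and the first scan with it. Such an analysis commonly sits in the analysis plan; its absence from the article is not the fault, but it is the only repair for patients already scanned.
- Report scan counts by arm.

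Equal intervals brought the simulated two-sided error to 0.047–0.057, with power 0.81 at 14/14.

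The cost is an amendment to Table 3 and the statistical section, with the approvals and registry updates of section {25}. Event times become coarser. A repeat scan is occasionally needed where an unscheduled one already showed resolution. Visits after discharge, now at least monthly (section {18b}), must be aligned with the scan days.

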### Plans to promote participant retention and complete follow-up {18b}

The enrolled patients will undergo all interventions on an inpatient basis and will be requested to visit the outpatient clinic at least once a month after the discharge. When patients do not make a scheduled visit, the investigators will call the patients to follow up on the patients’ conditions and make a subsequent appointment.

### Data management {19}

The investigators will upload collected patient data to the online storage. The data manager will download and integrate the files and then store the integrated database in a password-locked stand-alone computer at the research management office at The University of Tokyo Hospital (Tokyo, Japan). The data manager will also screen for missing or unplausible data and ask the corresponding investigator at each centre for data check. The document of data management procedures has been approved by the institutional review board at The University of Tokyo Hospital.

### Confidentiality {27}

A fake ID number will be assigned to each potential or enrolled participant, and all patient data will be anonymised as soon as they are collected. The corresponding investigator at each centre will store the list matching the fake and hospital ID numbers in a password-locked stand-alone computer.

### Plans for collection, laboratory evaluation and storage of biological specimens for genetic or molecular analysis in this trial/future use {33}

n/a. In the present trial, biospecimens will not be collected for genetic or molecular analyses.

## Statistical methods

### Statistical methods for primary and secondary outcomes {20a}

In the primary analysis, we will compare times to clinical success between the immediate necrosectomy and step-up approach groups. In our primary hypothesis testing, cumulative survival probabilities of times to clinical success will be estimated using the Kaplan–Meier product-limit method and be compared using the log-rank test. Patients are censored at the time-point of salvage surgery, the last follow-up, 6 months of the randomisation, or death, whichever came first. In the secondary analyses, we will use Student’s *t*-test or Wilcoxon rank-sum test, as appropriate, for continuous variables; the chi-square test or Fisher’s exact test, as appropriate, for categorical variables; and the log-rank test for time-to-event variables.

The two-sided α level of 0.05 was used for statistical significance for all analyses. All analyses will be conducted for the intention-to-treat population, and examinations of per-protocol population will represent secondary analyses.

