## Introduction

### Background and rationale {6a}

Pancreatic fluid collections develop as late complications of severe acute pancreatitis [1]. According to the revised Atlanta classification [2], walled-off necrosis (WON) has been defined as a collection characterised by encapsulated necrosis that is observed after four weeks of the onset of acute pancreatitis. Infected WON generally results in high morbidity and mortality, and it is mandatory to manage WON appropriately to improve clinical outcomes of patients with acute pancreatitis [3–6]. Endoscopic ultrasound (EUS)-guided drainage has become a first-line treatment modality for infected WON [7]. For patients who are refractory to EUS-guided drainage, direct endoscopic necrosectomy (DEN) is a treatment option to facilitate direct removal of infected necrotic tissue within the WON and thereby, control the infection [8]. Lumen-apposing metal stents (LAMSs) have emerged as a promising treatment modality in this setting and have increased the popularity of the non-surgical treatment through serving as a transluminal port for safe and effective DEN [9–12]. However, there is a controversy over the appropriate timing of starting DEN following EUS-guided drainage of WON [13–16]. Due to potentially lethal adverse events of DEN, such as bleeding, perforation, and peritonitis [8, 17, 18], DEN is usually initiated after several days of observation with unsuccessful clinical improvement (so-called the step-up approach). Given the adverse events related to DEN, many endoscopists may select the step-up approach consisting of intense drainage procedures (rather than DEN) including additional EUS-guided drainage through another route or addition of stents/catheters (termed “drainage-oriented step-up approach”) [19, 20]. However, prolonged duration of LAMS placement may result in stent-related adverse events (e.g. bleeding, buried stent, stent occlusion with or without fever) [21–24]. Recently, with increasing technical safety of DEN according to accumulated endoscopists’ knowledge and skills, studies suggest that DEN immediately after EUS-guided drainage potentially shortens treatment duration without a substantial increase in adverse events [14]. Given these lines of evidence, we hypothesised that immediate DEN following EUS-guided drainage of WON might shorten time to WON resolution compared to the drainage-oriented step-up approach.

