### Objectives {7}

The primary objective of the WONDER-01 trial is to evaluate the superiority of immediate DEN over drainage-oriented step-up approach following EUS-guided drainage of WON in terms of time to clinical success. The secondary objectives include assessments of a technical success rate, procedure-related adverse events, and long-term outcomes (detailed in Table 1).

**Table 1 Tab1:** The primary and secondary endpoints of the WONDER-01 trial

Primary endpoint	Secondary endpoints
Time from randomisation to clinical success^a^	Incidence of procedure-related adverse events graded by the AGREE classification [25] as well as the ASGE lexicon guideline [26]
Clinical success is defined as (1) a decrease in a WON size to 3 cm or less and (2) an improvement of at least two out of the three inflammatory markers (i.e. body temperature, white blood cell count, and C-reactive protein)	Mortality from any cause
	Technical success rate of the initial EUS-guided drainage
	Incidence of a biliary stricture and gastrointestinal obstruction
	Number of interventions
	Total procedure time
	Time requiring endoscopic and/or percutaneous drainage
	Length of hospitalisation
	Length of ICU stay
	Duration of antibiotics administration
	Total costs of interventions and hospitalisation
	Incidence of WON recurrence
	Time from clinical success to WON recurrence
	Incidence of a pancreatic pseudocyst
	Incidence of new-onset diabetes
	Incidence of clinical symptoms associated with pancreatic exocrine insufficiency
	Incidence of pancreatic cancer
	Incidence of sarcopenia
	Changes in the morphology and volume of the pancreas

^a^Patients who do not undergo clinical success within 6 months of the randomisation will be treated as cases with clinical failure

Abbreviations: *ASGE* American Society for Gastrointestinal Endoscopy, *EUS* Endoscopic ultrasound; *ICU*, Intensive care unit, *WON* Walled-off necrosis

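### The primary analysis censors death and salvage surgery, although the endpoint definition makes these patients failures; success is overstated, and the log-rank test can favour the arm with more such events

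*Protocol article*

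**What the plan says.** The section on statistical methods for primary and secondary outcomes {20a} says that times to clinical success "will be estimated using the Kaplan–Meier product-limit method and be compared using the log-rank test". It then fixes the censoring rule: "Patients are censored at the time-point of salvage surgery, the last follow-up, 6 months of the randomisation, or death, whichever came first". Death and salvage surgery are thus handled in the same way as loss to follow-up and the end of the 6-month window.

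The outcomes section {12} defines the status of patients without success differently: "Patients who do not undergo clinical success within 6 months of the randomisation are treated as cases with clinical failure". The footnote to Table 1 (objectives {7}) says the same. The outcomes section also names the headline summary: "The median time to clinical success will be used to evaluate the overall treatment efficacy of a given intervention".

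No competing-risk analysis, and no sensitivity analysis for death or surgery, appears in the sections on statistical methods {20a}, additional analyses {20b} or missing data {20c}. All-cause mortality is a secondary endpoint.

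**The concern.** The event here is a good outcome. Kaplan–Meier censoring assumes that a censored patient would go on to succeed at the rate of those still at risk. That is a fair working assumption for a patient who moves away. It cannot hold for one who has died, and it is doubtful for one sent to surgery because treatment was failing.

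A patient who dies on day 20 is a clinical failure under the outcomes section, yet leaves the risk set on day 20 under the analysis section. The two sections describe different quantities.

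Two consequences follow:

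- One minus Kaplan–Meier overstates the proportion who succeed and brings the median forward in any arm where these events occur.
- If the events are more frequent in one arm and remove its poor-prognosis patients, those left at risk in that arm look quicker to succeed.

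The document gives a reason why rates might differ. The background section describes the reluctance to start necrosectomy early: "Due to potentially lethal adverse events of DEN, such as bleeding, perforation, and peritonitis".

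**Working it through.** **Step 1. Reproduce the plan's sample size.** The inputs come from the sample size section {14}: success at 60 days "were 60% in the immediate necrosectomy group and 35% in the step-up approach group", 36 months' accrual, 6 months' follow-up, and "64 patients were required with a two-sided α level of 0.05 and a power of 0.80".

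- Exponential hazards, λ = −ln(1 − success)/60: immediate necrosectomy −ln(0.40)/60 = 0.01527 per day; step-up −ln(0.65)/60 = 0.00718 per day. The ratio is 2.127. The medians (ln 2/λ) are 45.4 and 96.5 days.
- Lachin–Foulkes: n per arm = [1.96√(2φ(λ̄)) + 0.842√(φ(λ₁)+φ(λ₀))]² / (λ₁−λ₀)², where φ(λ) = λ²/P(λ) and P(λ) is the event probability under uniform accrual. P is 0.996, 0.966 and 0.990 for λ₁, λ₀ and their mean.
- Result: 31.7, so 32 per arm and N = 64, as stated. This calculation has no separate term for death or surgery.

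**Step 2. Overstatement of success.** Take the step-up hazard λ = 0.00718, T = 182.6 days, and a constant hazard h of death or surgery, independent of success and chosen to give the assumed 6-month rate.

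- One minus Kaplan–Meier: 1 − e^(−λT) = 73.0%, whatever h is.
- True incidence: λ/(λ+h) × (1 − e^(−(λ+h)T)). At 15%, h = 0.00165 and λ+h = 0.00883, giving 0.813 × 0.801 = 65.1%.
- Median from the incidence curve: −ln(1 − 0.5/0.813)/0.00883 = about 108 days, against 96.5 days from Kaplan–Meier.

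| Death or surgery by 6 months (assumed) | 1 − KM | True success |
|---|---|---|
| 5% | 73.0% | 70.4% |
| 10% | 73.0% | 67.8% |
| 15% | 73.0% | 65.1% |
| 20% | 73.0% | 62.3% |

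**Step 3. Effect on the log-rank test.** Simulation with 35 per arm and the same underlying success times in both arms (hazard equal to the mean of the two design hazards, median 62 days). Death or surgery falls on days 3–45. A false win means that the arm with the first-listed rate is declared faster at two-sided 0.05 (nominal 2.5%). Ranges cover repeated runs.

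| Rates (assumed) | Who is affected | Planned rule | Failures kept to 6 months |
|---|---|---|---|
| 5% v 5% | slowest 30% | 2.6–2.8% | 2.8% |
| 10% v 5% | slowest 30% | 4.7–4.8% | 1.8–1.9% |
| 15% v 5% | slowest 30% | 7.7–8.5% | 1.2–1.3% |
| 20% v 5% | slowest 30% | 14.9–15.8% | 0.9% |
| 15% v 5% | slowest 50% | 4.6–5.0% | 0.8% |
| 15% v 5% | slowest 70% | about 3% | 0.5% |
| 15% v 5% | unrelated to success time | 2.6–2.9% | 0.6% |

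In the 15% v 5%, slowest-30% row, true 6-month success is lower in the arm with more events (78.5% v 84.3%). Reversing the rates to 5% v 15% reverses the bias: false wins for the first arm fall to 0.6–0.7%.

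A second model, in which a quarter of patients cannot succeed and only they die or have surgery, gives equal true success in both arms (54.8%). The planned rule then gives false wins of 6.4% at 15% v 5% and 10.4% at 20% v 5%. Keeping failures at risk to 6 months returns this to 2.4–2.6%.

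**Step 4. Power.** With the design hazards, 70 patients, every patient censored at 6 months and no deaths or surgery, simulated power is 82%. At 5% v 5% it is about 78–80% under the planned rule and about 68–75% with failures kept, depending on which patients are affected. At 15% v 5%, with events independent of success, it is 78% against 39%. In that case the true difference in 6-month success has itself shrunk, to 81.3% v 70.4% from 93.9% v 73.0% without such events.

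**The case against.** A reader might infer that any excess of deaths or surgery under immediate necrosectomy biases the result towards it. The documents do not support that, for three reasons.

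- Excess harm alone is not enough. If death and surgery are unrelated to the chance of success, the log-rank test remains valid for the cause-specific success hazard, and harm is ignored rather than rewarded. Bias also needs the removed patients to be those with poor prospects. That is plausible for salvage surgery, but no section shows it.
- The direction is open. The background section also reports studies suggesting that immediate necrosectomy shortens treatment without a substantial rise in adverse events. Salvage surgery could be commoner in the step-up arm, and the bias would then work against immediate necrosectomy.
- The 8% figure requires half of the slowest 30% in one arm (15/30) to die or have surgery by day 45. Milder assumptions give much less.

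It is also tempting to say that surgery makes success impossible. The definition rests on cavity size and inflammatory markers and does not require an endoscopic route, so a patient could meet it after surgery. Counting surgery as failure is an estimand choice.

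Finally, administrative censoring at 6 months is compatible with the failure label, and separate reporting of mortality would make excess deaths visible.

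All of this stands, and it limits the size and direction of the claim. It does not remove the conflict between the sections, correct the overstated success and shortened median, or protect the primary test when rates differ.

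**Conclusion.** The concern holds in a conditional form. The early censoring of death and salvage surgery contradicts the plan's own failure rule. It overstates success whenever such events occur: 73.0% reported against 65.1% true at an assumed 15%, with the median about 12 days too early (108 − 96.5).

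Distortion of the primary test needs two further conditions: unequal rates, and events falling on poor-prognosis patients. At an assumed 15% v 5%, the false-win rate for the arm with more events then runs from close to the nominal 2.5% (no link with prognosis) through about 5% (slowest half) to about 8% (slowest 30%). With equal rates the test is not distorted. All rates of death and surgery are assumptions, since the documents give none, and which arm would benefit is unknown.

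**What to change.** Reconcile the analysis section {20a} with the outcomes section {12} and the Table 1 footnote:

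1. Keep patients who die before success in the risk set as non-successes to 6 months.
2. State explicitly that salvage surgery is handled in the same way, as failure of the allocated strategy. If patients are instead to be followed for success after surgery, say so, because that is a different estimand.
3. Report cumulative incidence of success (Aalen–Johansen) with death and salvage surgery as competing events, take the median from that curve, and test with Gray's test.
4. Keep the cause-specific log-rank test as a sensitivity analysis.
5. Censor early only for true loss to follow-up.

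The change needs a short amendment, made before the analysts see the allocation. It uses standard software and no new data. The real cost is power: with 70 patients and 5% v 5% it falls from about 78–80% to about 68–75%, and further if immediate necrosectomy has more failures. The stated 80% should be restated for the revised analysis, with the assumed death and surgery rates given.

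### With no stated rule for death, the t-test or rank-sum comparison of hospital stay, ICU stay and antibiotic duration could show an excess of early deaths as a shorter stay (minor, secondary endpoints)

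*Protocol article*

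**What the plan says.** Table 1 (Objectives {7}) lists "Length of hospitalisation", "Length of ICU stay", "Duration of antibiotics administration" and "Time requiring endoscopic and/or percutaneous drainage" among the secondary endpoints. "Mortality from any cause" is a separate secondary endpoint, with no expected rate.

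The section on statistical methods {20a} assigns Student's t-test or "Wilcoxon rank-sum test, as appropriate, for continuous variables", and "the log-rank test for time-to-event variables", without saying which endpoints fall in which group. It makes the intention-to-treat population the basis of all analyses, with per-protocol analyses as secondary.

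Death is handled explicitly only for the primary endpoint: "Patients are censored at the time-point of salvage surgery, the last follow-up, 6 months of the randomisation, or death, whichever came first". The section on missing data {20c} drops a patient from a secondary analysis when that variable is missing. It does not say whether death makes a duration missing.

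**The concern.** A stay that ends in death is a complete recorded value, and after an early death it is a short one. A rank-sum test or t-test on recorded stays puts that patient among the best results, and the same holds for ICU days and antibiotic days. The Background {6a} says that infected WON carries high mortality and that complications of DEN can be fatal. The arms differ in when and how often DEN is used, so unequal early mortality is a plausible safety scenario. In that scenario, three of the measures of patient burden would move in favour of the arm with more deaths.

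**Working it through.** **Inputs from the article.** 35 patients per arm (Sample size {14}), the rank-sum test, and a two-sided α of 0.05 ({20a}). The article states no mortality rate, stay distribution or time of death, so there is no figure of its own to reproduce here. Everything below is an illustration on assumed values. The t-test was not simulated.

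**Direction, by arithmetic.** Let mortality be m1 and m2, with the same stay distribution for survivors in both arms. Suppose that every death leaves a shorter recorded stay than every survivor's. Take one patient from each arm, counting a tie as one half. The chance that the patient from arm 1 has the shorter stay is

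m1(1 − m2) + ½[m1·m2 + (1 − m1)(1 − m2)] = ½ + ½(m1 − m2).

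This is 0.525, 0.550 and 0.575 for 10%, 15% and 20% v 5%, and exactly 0.5 at equal mortality. With deaths ranked worst the sign flips, to ½ − ½(m1 − m2), which is 0.475, 0.450 and 0.425.

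**Size, by simulation.** A result is falsely favourable when the two-sided rank-sum test gives p < 0.05 with the shorter stay in the arm with more deaths, although the underlying stay is the same in both arms. The nominal rate is 2.5%.

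*Assumption set A.* Lognormal stay with median 45 days and log-SD 0.6. A death replaces the stay with a value drawn between 5 and 25 days. The ranges cover three separate runs of the raw-stay comparison, the largest of 6,000 trials per setting.

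| Mortality | Raw stay | Deaths ranked worst |
|---|---|---|
| 10% v 5% | 4.4 to 5.2% | 1.0% |
| 15% v 5% | 8.7 to 9.8% | 0.3% or less |
| 20% v 5% | 15.8 to 16.8% | 0.2% or less |

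*Assumption set B.* Lognormal stay with median 40 days and log-SD 0.7; time to death has a median of 14 days. There were 6,000 trials per setting.

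| Mortality | Mean difference in stay | Raw stay | Deaths ranked worst |
|---|---|---|---|
| 5% v 5% | 0.0 days | 2.2% | 2.5% |
| 10% v 10% | −0.1 days | 2.4% | 2.5% |
| 10% v 5% | −1.9 days | 4.5% | 0.8% |
| 15% v 5% | −3.5 days | 8.3% | 0.5% |
| 20% v 5% | −5.5 days | 13.8% | 0.1% |

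In set B the simulated chance of a shorter raw stay was 0.52, 0.54 and 0.56 in the three unequal settings. That is slightly below the formula, because some survivors also leave early.

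**Timing of death.** Keep set A but move the deaths (6,000 trials per setting). With deaths spread over 5 to 90 days, the raw-stay rate is 2.6%, 2.8% and 2.7% for 10%, 15% and 20% v 5%, so the excess almost disappears. With deaths at 60 to 120 days it is 1.2%, 0.8% and 0.3%, so the effect reverses. The distortion needs both unequal mortality and early deaths.

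**Deaths involved.** The expected numbers are 35 × 0.05 = 1.75 in one arm against 3.5, 5.25 or 7 in the other, a difference of 1.75 to 5.25 deaths.

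**The case against.** The strongest objection is that this is silence, not error. A condensed article commonly leaves the scoring of deaths on secondary durations to the full protocol or the analysis plan, and neither is shown. That stands: the missing rule is not in itself a fault. What remains is how the named tests behave on the natural reading.

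A reader might infer that the plan counts an early death as a favourable stay. The article does not say so, and other readings are open. Some durations, the time requiring drainage for example, might be analysed by log-rank. Deaths might be treated as missing and dropped. Neither reading removes the need for a rule. Dropping deaths gives a survivors-only comparison, which sits badly with the intention-to-treat statement. A log-rank analysis must still either count death as the end of the stay or censor it as if uninformative.

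A reader might also infer that these endpoints carry the trial's rationale of reducing burden on patients and the health care system. The Outcomes section {12} gives that rationale for the primary endpoint, not for these durations.

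Two further points stand. Mortality is reported separately, so an imbalance would be visible, though that does not correct the duration tests. And what is spent on, or done to, a patient who later dies is a valid measure of resource use, so the point should not extend to costs or number of interventions.

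**Conclusion.** The point holds as a minor improvement to three secondary endpoints: length of hospitalisation, length of ICU stay and duration of antibiotics. If one arm has more early deaths, the named tests could show it as a shorter stay. On the assumed inputs, a falsely favourable result occurs in about 4 to 16% of trials against a nominal 2.5%, with an apparent shortening of roughly 2 to 5.5 days under the second set of assumptions. There is no bias at equal mortality, and the effect fades or reverses as deaths come later. The article gives none of the figures needed to say which case applies, so these rates do not predict what this trial will show. The primary analysis is not affected.

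**What to change.** For length of hospitalisation, ICU stay and antibiotic duration only, compare days alive and out of hospital, out of ICU or off antibiotics to 6 months from randomisation. Alternatively, keep the rank-sum test and give deaths the worst rank. Report raw durations descriptively beside mortality. Leave costs and number of interventions as they are.

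To see the effect, take 6 months as 182 days. An inpatient who dies on day 10 has a raw stay of 10 days, among the best values, but 0 days alive and out of hospital. A survivor with a single 45-day stay from randomisation has 182 − 45 = 137.

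The wording takes a sentence or two and should be settled before the unblinded analysis. The cost is that the summary becomes a composite with mortality and is less familiar than raw stay. Days out of hospital also need readmission dates to 6 months from the charts, and the article does not say whether its stay endpoint covers more than the index admission. The worst-rank version avoids that extra collection.
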